#### Echocardiography assessment of PPHN

All infants will undergo a comprehensive echocardiography assessment at baseline prior to enrollment to rule out congenital heart disease, quantify the magnitude of pulmonary hypertension and assess left and right ventricular output and function. The functional protocol for the echocardiography assessment is adapted from the recent American Society of Echocardiography Guideline on neonatal echocardiography [31, 32]. All infants will be assessed once established on iNO and are in a quiet state using the Vivid E9 or the Vivid S6 (GE Medical, Milwaukee, WI, USA) and a 10 Mhz transducer. A diagnosis of PPHN will be made if any of the following is identified in the absence of cyanotic congenital heart disease:A tricuspid regurgitant jet with a pressure gradient ≥^2^/_3_ systemic systolic blood pressureIntra-ventricular septum flattening or bowing into the left ventricular cavityPatent ductus arteriosus bidirectional shunting or predominant right to left shuntingA pulmonary artery acceleration time < 40 milliseconds

We will collect the following parameters at the same time points outlined in section “Monitoring, outcome measures and participant timeline”:*Assessment of pulmonary Hypertension*: PDA Shunt Direction; Pulmonary artery acceleration time (PAAT); Right ventricular ejection time (RVET); PAAT:RVET ratio; Tricuspid regurgitant jet pressure gradient; Interventricular septum motion in systole.*Assessment of RV performance*: Right ventricular tissue Doppler velocities, strain and strain rate; Right ventricular output (RVO); Right ventricular TAPSE (Tricuspid Annular Peak Systolic Velocity); Right ventricular dimensions; Right ventricular fractional area shortening.*Assessment of LV performance*: Shortening fraction; Ejection fraction measured by Simpson’s biplane method; Tissue Doppler velocities; Left ventricular strain and strain rate; Left ventricular output (LVO); Left ventricular twist, and twist/untwist rate.*Assessment of Pulmonary venous return*; Left atrial to aortic root ratio; Pulmonary vein peak systolic and diastolic velocity; Mitral valve E and A velocities, E:A ratio, and mitral value VTI, IVRT; The presence of PFO/ASD and the velocity of the shunt.*Assessment of PDA parameters*: PDA size in 2D measured at the pulmonary end, mid ductal and aortic end; the direction and peak velocity of flow across the shunt; Pressure gradient across the shunt.*Markers of systemic hypoperfusion*: Abdominal aortic peak systolic velocity and diastolic flow direction and velocity; Celiac artery peak systolic velocity and diastolic flow direction and velocity; Middle cerebral artery peak systolic velocity and diastolic flow direction and velocity.

Reliability analysis was recently conducted and ascertained normative data for all the above-mentioned echocardiography parameters in 50 healthy term infants. Acceptable reliability was demonstrated in measuring all the functional parameters. In addition, the reference ranges and the effect of physiological postnatal transition is described [33].

Slow closure of the patent ductus arteriosus is a theoretical risk in association with the use of milrinone due to the drug’s vasodilatory properties. However, in our observational study of 17 infants (section 1.2.3), none had a patent ductus arteriosus by the time of discharge despite the relatively longer duration of milrinone use in the observational study (median of 88 h). We will assess the presence of patent ductus arteriosus before discharge on all infants enrolled to further study this association.

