### The relevance of the primary outcome

iNO use is expensive and currently requires invasive ventilation. Invasive ventilation can cause baro- and volutrauma, may lead to parenchymal lung damage and the evolution of pneumothoraces. Ventilation is often accompanied by the administration of sedative agents such as morphine and midazolam. In addition, prolonged ventilation will delay bonding with parents, delay feeding and suckling and will lead to prolonged hospitalisation. A reduction in the time spent invasively ventilated will (in addition to the other benefits outlined above) reduce hospital stay, promote earlier enteral nutrition, parental bonding, breast feeding and significantly reduce healthcare costs.

The purpose of this pilot study is to assess the feasibility of performing a pivotal trial and to obtain preliminary data to calculate a sample size for a definitive multi-centre trial of milrinone therapy in PPHN. We aim to recruit a total of 20 infants with PPHN (10 receiving milrinone and 10 receiving placebo) over a 4-year period. We then plan to seek additional funding in order to facilitate the running of the multicentre RCT in European and North American centres. In this pilot study we also aim to ascertain issues with recruiting infants and obtaining consent, compliance with the protocol, the rate (if any) of loss to follow up, and the general acceptability, feasibility and compliance of administering the intervention. This number will also allow us to calculate a standard deviation which will be used in a sample size calculation for the full-scale trial. In addition, we aim to refine the criteria for discontinuing therapy which are outlined below.

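### Slow ductal closure is studied through duct patency before discharge, which is insensitive to a delay that resolves and is taken at a treatment-dependent age, while the serial duct data already collected are not linked to the question

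*Protocol article*

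**What the plan says.** All places are in the protocol article.

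- **Echocardiography assessment of PPHN** states the risk: "Slow closure of the patent ductus arteriosus is a theoretical risk in association with the use of milrinone". It then offers reassurance from an observational cohort of 17 infants, in which "none had a patent ductus arteriosus by the time of discharge despite the relatively longer duration of milrinone use" (median 88 h). It ends with the measure chosen for the trial: "We will assess the presence of patent ductus arteriosus before discharge on all infants enrolled to further study this association". No postnatal age is attached to that assessment.
- **The same section** lists duct measurements for all infants at the scheduled scans, including "PDA size in 2D measured at the pulmonary end, mid ductal and aortic end", together with flow direction, peak velocity and pressure gradient. They are listed as echocardiographic parameters and are not connected to the closure question.
- **Monitoring, outcome measures and participant timeline** gives two scan schedules. One is baseline, 12 h, 24 h and 8 h after stopping study drug, and the cardiac output monitoring text calls that 8 h scan the last one. The other is baseline, 12 h, 24 h, 2 h after stopping and before discharge.
- **Intervention** caps therapy at 35 h.
- **The relevance of the primary outcome** expects less ventilation to "reduce hospital stay, promote earlier enteral nutrition". Duration of hospital stay is a secondary outcome.

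**The concern.** The harm is a delay, and the measure chosen for it cannot register a delay that ends before the infant goes home. The group's own experience, with much longer exposure than this trial allows, suggests the proportion open at discharge will be low in both arms. A null result on this measure would then say little about closure time.

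The time of measurement also depends on treatment. If milrinone shortens stay, as the article hopes, treated infants are scanned younger. Ducts close with age, so more would be open in that arm with no drug effect on the duct.

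Two smaller gaps follow. Infants who die have no pre-discharge scan, although the text says all enrolled infants. And the PPHN definition is met by any one of four signs, only one of which requires an open duct, with entry allowed up to 10 days of age. Some ducts may therefore be closed at baseline and cannot inform a comparison of closure.

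At stake is how the pilot's evidence on one named safety risk is read when the definitive trial is planned. The primary outcome and the feasibility aims are not affected.

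**Working it through.** The article gives no power or event calculation for ductal closure, so there is no planned figure to reproduce. The only figure is 0 of 17.

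**1. What 0 of 17 allows** (taking all 17 as assessed). One-sided 95% upper limit: 1 − 0.05^(1/17) = 16.2%. Two-sided: 1 − 0.025^(1/17) = 19.5%. A low proportion is expected, but zero is not established. The 35 h cap here is 35/88 = 40% of that cohort's median exposure.

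**2. What 10 per arm can show on a yes/no measure.** With 0 of 10 open on placebo, the two-sided Fisher p-value is 0.087 for 4 of 10 open on milrinone and 0.033 for 5 of 10. The chance of at least 5 of 10 is 1.4% at a true 16.2%, 3.0% at 19.5% and 15.0% at 30%. If 0 of 10 are open in an arm, the one-sided 95% upper limit is 1 − 0.05^(1/10) = 25.9%.

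**3. Insensitivity to a delay (illustration).** Assume exponential closure, so the proportion open on day t is 0.5^(t/m), where m is the median closure time. Neither the form nor the medians come from the article. Let m be 2 days on placebo and 4 days on milrinone.
- Both arms scanned on day 4: 0.5^(4/2) = 25% v 0.5^(4/4) = 50% open.
- Both arms scanned on day 14: 0.5^(14/2) = 0.8% v 0.5^(14/4) = 8.8% open.

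On day 14 the chance of no open duct in either arm is 0.992^10 × 0.912^10 ≈ 0.37, although closure time has doubled. Power by Fisher's test is 0.1% on day 14 and only about 9% on day 4.

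**4. Effect of age at scan alone (illustration, no drug effect on the duct).** Same formula and the same m in both arms, with milrinone infants discharged earlier. Medians and discharge days are assumptions.

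| Assumed median closure | Placebo day 14 v milrinone day 10 | Placebo day 10 v milrinone day 7 |
|---|---|---|
| 2 days | 0.8% v 3.1% | 3.1% v 8.8% |
| 3 days | 3.9% v 9.9% | 9.9% v 19.8% |
| 4 days | 8.8% v 17.7% | 17.7% v 29.7% |

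The spurious difference runs from about 2 to 12 percentage points, always towards apparent harm. The larger entries fit the earlier cohort poorly: at a true 17.7% the chance of 0 of 17 is 0.823^17 ≈ 3.7%; at 8.8% it is 0.912^17 ≈ 21%. That cohort's discharge ages are not in the article, so this is a plausibility check only.

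**5. What the serial scans cover.** With the 35 h cap, the post-infusion scan falls at the latest about 35 + 2 = 37 h or 35 + 8 = 43 h after the start, depending on the schedule and before the ±3 h window. No scan is scheduled between then and discharge.

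**6. Infants without a pre-discharge scan.** The introduction cites PPHN mortality of 4% to 33%. Applied to 20 infants for illustration only, that is 0.8 to 6.6, or roughly 1 to 7.

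**The case against.** The strongest reply is that the pre-discharge check is not the only look at the duct. Size at three sites, direction, velocity and gradient are recorded at baseline, 12 h, 24 h and after stopping. The 12 h and 24 h scans are timed from study drug, so earlier discharge cannot move them. The text does not exclude these data from the closure question. This stands. A reader might infer that a delay would simply be missed; the documents do not support that.

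Second, the power figures reflect 10 per arm rather than a poor measure. Any binary outcome would need 5 v 0, and a fixed day-4 scan reaches only about 9% power in the illustration. This also stands.

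Third, the two mechanisms pull against each other: if almost no ducts are open at discharge, age at scan hardly matters. The age bias is therefore conditional on some ducts being open, and its size rests wholly on assumed closure and discharge times.

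Fourth, no passage says that the pilot will conclude there is no association, and the age bias would not hide a harm because it points the other way. Both are correct.

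Fifth, analysis detail for a secondary safety measure normally sits in the full protocol or analysis plan, which are not shown. This stands for the choice of model. It does not dispose of the point, because the article does fix a measure for a named risk, and that measure suits the risk badly.

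**Conclusion.** The concern holds in limited form. The only measure the article ties to slow ductal closure is patency before discharge. It is insensitive to a delay that resolves by then, and its timing depends on a stay that treatment is expected to shorten. The first part rests on the article's own wording and its 0 of 17 (upper limit 16% one-sided, 19.5% two-sided). The direction of the age bias needs only that ducts close with age and that milrinone infants leave earlier. Its size, about 2 to 12 points in the scenarios shown, is assumption throughout.

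The documents do not show that delayed closure will go undetected, that a false reassurance will be issued, or that age at scan will matter if no ducts are open. The serial duct data exist but are not linked to the question. This is a small improvement to a secondary safety assessment.

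**What to change.** In the paragraph on ductal closure, state that:

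- ductal patency and diameter will be summarised and compared by arm at each scheduled scan, accounting for baseline patency or diameter;
- the pre-discharge proportion will be reported with postnatal age at that scan and the number of infants without one, including deaths;
- results will be descriptive, with confidence intervals, and zero open ducts at discharge will not be read as absence of delayed closure.

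Time-to-closure modelling is optional; with 20 infants and the gap between the post-infusion and pre-discharge scans it would add little.

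Separately, reconcile the two echocardiography schedules under Monitoring, outcome measures and participant timeline. Only one of them contains the pre-discharge scan on which this assessment depends.

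The cost is a change of wording and slightly more secondary analysis, with no new measurement. Precision will stay low at 10 per arm.

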#### Non-invasive cardiac output assessment (NICOM)

Non-invasive cardiac output monitoring has gained interest in the assessment of neonatal haemodynamics [34, 35]. Trans-thoracic bioreactance is a new technique of non-invasive continuous cardiac output monitoring. It is based on an analysis of relative phase shifts of oscillating currents that occur when an injected current traverses the thoracic cavity. The system’s signal processing unit determines the relative phase shift (Φ) between the input and output signals. Stroke volume (SV) can be estimated by: SV = C x VET x dΦ/dtmax, where C is a constant of proportionality, VET is ventricular ejection time (determined from the NICOM and ECG signals) and dΦ/dtmax is the peak rate of change of Φ.

The value of C has been optimized in prior studies and accounts for patient age, gender and body size. SV and left ventricular (LVO) measurement are provided in 60 s intervals [36]. In the adult population, NICOM has acceptable accuracy and precision for cardiac output monitoring in patients with hemodynamic instability when compared to thermodilution, aortic artery catheterisation, and cardiopulmonary bypass pumps [36–38]. Recently, NICOM was compared to echocardiography measures of LVO in a cohort of near term and term neonates with acceptable reliability and precision [35]. In addition, NICOM has the ability to identify different haemodynamic patterns and response to milrinone administration in preterm infants following PDA ligation [35]. These properties suggest that NICOM may be an ideal device for the assessment of the haemodynamic profile of infants with PPHN.

Continuous LVO measurement using bioreactance is facilitated by the NICOM system. The measurement will take place during the entire study period. Bioreactance is the analysis of the variation in the frequency spectra of a delivered oscillating current when it traverses the thoracic cavity. This is obtained by placing four emitting and receiving electrodes in a manner that “boxes” the heart. Each electrode sensor strip consists of two contact points. Upper thoracic electrode strips will be placed over the mid-clavicles and upper back bilaterally. The lower electrode sensors are placed between the 6th and 7th intercostal spaces at the mid-axillary line. The electrode set will be replaced after 48 h of measurement to ensure adequate signal acquisition. NICOM measurement of SV and LVO will be blinded to the echocardiography and the clinical team by covering the screen displaying the values. The echocardiographic measurement of SV and LVO will be paired with the corresponding NICOM readings following study completion. The NICOM system stores each reading of SV and LVO. SVR will be measured by the NICOM system on an hourly basis as the mean blood pressure is entered into the machine.

### Data management and statistical analysis

#### Sample size

This study is conducted to determine the feasibility of patient recruitment, instituting the study protocol, randomising and blinding allocation, collecting outcome data and contribute to determine the sample size necessary for a definitive multicentre trial. A sample of 10 infants per arm (a total of 20 infants) will be recruited over a 4-year period.

#### Recruitment strategies

The recent incidence of pulmonary hypertension in the three study sites is 1–2 per 1000 live births. The total annual birth rate in the 3 centres is around 24,000 giving 24–48 potential eligible infants. The rate of moderate to severe PH in this cohort (fulfilling the eligibility criteria) will be around 50% (12–24 infants per annum). We anticipate a 50% to 75% enrolment rate per year to account for consent refusal, competition with other studies and unavailability of staff to recruit patients. Therefore, we anticipate a recruitment period of 4 years. All centres are experienced in the conduct of clinical trials. They also have the expertise to carry out the assessment of the primary and secondary outcomes and to perform the echocardiography and NICOM assessments. We do not anticipate any variability in administering the intervention between sites over time.

#### Data management

Clinical and demographic data, as well as outcome data will be collected by the research fellows at each site who will be blinded to treatment allocation. Pilot testing of the data collection sheet will be performed prior to study commencement. No patient identifiers will be used and each patient will be assigned a unique ID number based on the sequence in recruitment. The data sheets will be stored in a designated secure locker with access granted only to the research fellows and principal investigators. Echocardiography data will be stored on secure hospital servers. Off-line analysis of the echocardiography data will be performed and image analysis techniques will be standardised. The investigators analysing the study will be blinded to the allocation.

#### Statistical methods

The HRB IP CTN clinical trial statistician will conduct all the statistical analyses. The primary outcome and most of the secondary outcomes are continuous variables. Continuous variables will be tested for normality by comparing the mean and median, a histogram representation of data, and the Shapiro-Wilk test for normality and will be presented as means (standard deviation) or median [inter-quartile range] as appropriate. Dichotomous variables will be presented as proportions and summarised in contingency tables. The *primary analysis of the primary outcome* will be performed using an independent t-test (or a Wilcoxon Rank Sum test as appropriate) to compare the difference in time on iNO and invasive ventilation between the two groups. A chi squared test (or Fisher’s exact test) will be used for the *primary analysis of the dichotomous secondary* outcomes. For the continuous secondary outcomes, a t-test will be used to compare normally distributed data, and Wilcoxon Rank Sum test will be used for skewed data. We will accept a *p* value of < 0.05 as significant. We will use SPSS (version 22) to perform the statistical analysis.

All enrolled infants will be analysed on an intention-to-treat basis, including infants that have not continued treatment for any reason. Analysis for the feasibility study will only be conducted once the recruitment of all patients is completed. No interim analysis of treatment effect will be conducted. We anticipate that recruitment will take 4 years to complete with an additional 6 months required for the measurement of the echocardiography data and statistical analysis.

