## Introduction

### Scope of the problem

Persistent pulmonary hypertension of the newborn (PPHN) is a relatively common condition occurring in 0.5 to 7 per 1000 live births and results in a mortality ranging between 4 to 33% [1, 2]. Inhaled nitric oxide (iNO) and extracorporeal membrane oxygenation (ECMO) are the only current therapeutic options that are systematically evaluated in clinical trials [3, 4]. The vasodilatation induced by iNO is mediated by increasing concentrations of the second messengers: cyclic guanyl monophosphate (cGMP) and cyclic adenosine monophosphate (cAMP) in pulmonary vascular smooth muscle. The widespread use of iNO has resulted in a reduction in the need for ECMO; however, mortality and long-term morbidity remain unchanged [1, 4]. In addition, up to 40% of infants treated with iNO either have a transient response or fail to demonstrate an improvement in oxygenation [4, 5]. iNO does not improve myocardial performance in infants with PPHN, which often accompanies the condition and may contribute to mortality. Furthermore, the increasing cost of administering iNO to infants with PPHN may prohibit its use in developing countries. Due to these challenges, there is a real need to evaluate novel approaches to the management of PPHN.

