### Rationale for milrinone use

PPHN is common and leads to a major burden of neonatal illness, carries a significant mortality, need for ECMO, and adverse neurodevelopmental outcome. There is poor appreciation of the physiologic determinants of PPHN and predictors of iNO response at presentation; up to 40% of infants do not respond to iNO treatment. The increasing cost of iNO may preclude its use in both the developed and developing countries. The use of milrinone in infants with PPHN as an adjunct to iNO is worth further exploration with preliminary evidence suggesting an improvement in both oxygenation and myocardial performance in this group of infants. It’s inotropic, lusitropic and pulmonary vasodilator properties make it an ideal agent to use in this setting and may improve response to therapy and reduce mortality associated with the disease.

A recent Cochrane review illustrated the lack of randomised controlled trials (RCTs) comparing the use of milrinone versus placebo or as an adjunct to iNO compared with iNO alone in the setting of PPHN and recommended limiting the use of milrinone in PPHN to the research setting [29]. It is important to systematically investigate the efficacy of milrinone in the setting of PPHN prior to widespread dissemination of this treatment.

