#### Monitoring, outcome measures and participant timeline

The primary outcome of this study is the time on iNO in hours and the time on invasive ventilation. A standardised protocol for iNO weaning is detailed in Additional file 2.

We will collect the following demographic characteristics and relevant short-term secondary outcomes: duration of hospital stay; time to extubation; duration of oxygen therapy, and survival.

**Details of cardiorespiratory stability** (blood pressure, heart rate, oxygen saturation), ventilation support (FiO_2_, mean airway pressure (MAP), oxygenation index [MAP × F FiO_2_/PaO_2_]), efficacy of oxygenation [PaO_2_], plasma lactate, pH, PCO_2_, HCO_3_^−^, Base excess; and relevant co-treatments (i.e., sedation, analgesics, muscle relaxants, inotropes, fluid administration) at the following time points:Prior to treatmentFollowing the loading dose12 h after initiation of therapy24 h after initiation of therapyTwo hours after discontinuation of therapy

**Monitoring of blood parameters** will be carried out as follows during the study period and 24 h after drug discontinuation:Full blood count (including platelets): dailyElectrolytes, Urea and Creatinine: dailyLiver function tests (ALT, AST, GGT): dailyBlood gas analysis: 12 hourly

**Echocardiography** will be performed according to the following schedule: a timing window of ±3 h will be applied. Scans performed outside the ±3 h window will constitute a protocol deviation:Prior to the Commencement of Study Drug: Diagnose PPHN and rule out CHD12 h following the administration of Study Drug24 h following the administration of the study drug8 h following the discontinuation of the study drug

**Non-invasive Cardiac output Monitoring (NICOM)** will be commenced prior to the commencement of the study drug and continued until the last echocardiogram, 8 h after the discontinuation of the study medication.

**Cranial ultrasound** will performed prior to treatment commencement and after the discontinuation of the infusion. Intraventricular haemorrhage will be defined and graded with the Papile classification [30]. Echocardiography will be carried out at baseline as detailed above and at 12 h, 24 h, 2 h after discontinuation of therapy, and before discharge.

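### Raw hours on iNO and on ventilation are compared in all infants with no rule for death, so an infant who dies early is scored as a short, favourable duration

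*Protocol article*

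**What the plan says.** Under Monitoring, outcome measures and participant timeline, the article defines the endpoint: "The primary outcome of this study is the time on iNO in hours and the time on invasive ventilation". The same section lists the short-term secondary outcomes as "duration of hospital stay; time to extubation; duration of oxygen therapy, and survival". Survival therefore stands beside the durations and is not linked to them.

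Statistical methods classes the primary outcome as continuous and names a t-test, or a Wilcoxon rank sum test where suitable, as its primary analysis, "to compare the difference in time on iNO and invasive ventilation between the two groups". It then fixes the analysis set: "All enrolled infants will be analysed on an intention-to-treat basis, including infants that have not continued treatment for any reason".

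The article expects deaths in this disease. Scope of the problem says that PPHN "results in a mortality ranging between 4 to 33" per cent, and Rationale for milrinone use says that it "carries a significant mortality, need for ECMO, and adverse neurodevelopmental outcome". No section says what duration is assigned to an infant who dies or goes to ECMO. The article gives no worst rank, event-free time, competing-risk method or restriction to survivors.

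**The concern.** Time on iNO and time on a ventilator end for two opposite reasons: the infant recovers, or the infant dies. A test on raw hours cannot tell these apart. An infant who dies on the first day contributes a value of a day or less, among the best in the trial.

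Three things are at stake. First, an excess of early deaths in one arm would make that arm look better on the primary outcome. Second, Statistical methods accepts p < 0.05 as significant, and the Conclusion says a positive result would lead to a definitive trial, so the primary comparison will be read for direction even though this is a pilot. Third, The relevance of the primary outcome says the standard deviation from this study will feed the next trial's sample size. That SD would mix completed courses with courses cut short by death.

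Hospital stay, oxygen duration and time to extubation have the same defect.

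**Working it through.** **Inputs from the article.** Sample size: "A sample of 10 infants per arm (a total of 20 infants) will be recruited over a 4-year period". Mortality: 4% to 33% (Scope of the problem), a range for PPHN in general. The article gives no power, effect size or SD, so it has no figure of its own to reproduce here.

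**Step 1: how many deaths to expect.**
- Expected deaths: 20 × 0.04 = 0.8 and 20 × 0.33 = 6.6.
- At least one death among 20: 1 − 0.96^20 = 56% and 1 − 0.67^20 = 99.97%.
- At least one death in a given arm of 10: 1 − 0.96^10 = 34% and 1 − 0.67^10 = 98%.

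**Step 2: chance imbalance with no effect on mortality.** Take the two arms' death counts as independent binomials with n = 10.
- At 4% in both arms, the counts differ by one or more with probability 48%, and by two or more with probability 8%.
- At 10% in both arms, these are 69% and 24%.

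**Step 3: what one early death does to an arm mean.** If survivors average m hours and one of ten infants dies at 24 h, the mean shifts by (24 − m)/10. For an assumed m of 72 to 120 h, this is −4.8 h to −9.6 h, in the favourable direction.

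**Step 4: effect on the comparison.** None of these inputs is in the article: survivors' time on iNO lognormal with median 72 h and log-SD 0.7; no drug effect in survivors; duration equal to time of death in those who die.
- Survivor mean: 72 × exp(0.7²/2) = 92.0 h.
- Mean difference = (difference in mortality) × (mean time of death − 92.0).

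| Mortality, lower vs higher arm | Deaths at 12–48 h (mean 30 h) | Deaths at 48–240 h (mean 144 h) |
|---|---|---|
| 10% vs 30% | 0.20 × (30 − 92) = −12.4 h | 0.20 × (144 − 92) = +10.4 h |
| 4% vs 33% | 0.29 × (30 − 92) = −18.0 h | 0.29 × (144 − 92) = +15.1 h |

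A negative value favours the arm with more deaths. Simulation with 10 per arm agrees: for 10% vs 30% it gives −12.4 to −12.9 h with early deaths and +10.4 to +10.6 h with late deaths.

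Share of simulated trials in which the arm with more deaths has the shorter median, at 10% vs 30%:
- Raw durations, early deaths: about 71%.
- Raw durations, late deaths: about 35%.
- Death ranked worst: about 26–27%, whatever the timing of death.

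**Step 5: equal mortality.** At 4% in both arms and at 33% in both arms (a second set of assumptions: survivor median 90 h, log-SD 0.6, deaths at 6–48 h), the Wilcoxon test was significant in about 2% of trials in each direction. This held for raw durations and for death ranked worst, so neither is biased when mortality is equal.

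**The case against.** The strongest case on the other side has five parts.

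**Timing.** The direction of the bias depends on when infants die relative to weaning, and the article gives neither time. An infant who fails iNO and dies after days of support contributes a long duration. This stands: the last column of the table changes sign.

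**Mortality contrasts.** A reader might take 4% vs 33% as a plausible contrast between arms. It is not one. The range describes PPHN in general. The Exclusion Criteria remove cooled hypoxic-ischaemic encephalopathy, refractory diastolic hypotension and other high-risk infants, and the group's earlier cohort of 11 infants on milrinone had no deaths. Real contrasts may be much smaller: at 4% vs 8%, even with early deaths, the shift is 0.04 × (30 − 92) = −2.5 h. This stands against large effect sizes. It does not remove the problem, because even at 4% a death somewhere in the trial is more likely than not.

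**ECMO.** A reader might infer that transfer to ECMO also shortens the recorded durations. The article gives no ECMO rate and does not say whether either duration stops at ECMO, so the direction is unknown. Only the absence of a rule can be raised.

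**Detail for the analysis plan.** Coding of durations after death is often left to a statistical analysis plan or full protocol, and neither is shown. Here, however, the article itself fixes the endpoint, the tests and the analysis set. A plan that carried these out faithfully would reproduce the flaw.

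**Pilot status.** This is a 20-infant feasibility study, with survival reported and a data monitoring committee watching adverse effects. That limits the consequences, but a separate survival line does not change how the primary comparison scores a death.

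**Conclusion.** The point holds, with limits. As written, the primary comparison counts an early death as a short, favourable duration, and nothing in the article corrects this. At the cited mortality, at least one death among 20 infants has a probability of 56% to over 99.9%, subject to exclusions that may lower mortality below the cited range.

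The size of the distortion cannot be taken from the article. In the 10% vs 30% illustration with deaths at 12–48 h, it is a spurious mean benefit of about 13 h for the arm with more deaths, and that arm has the shorter median in about 71% of trials, against about 27% with death ranked worst. These figures rest on assumed survivor durations, times of death and mortality in each arm.

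A reader might infer that any treatment that raises mortality would appear beneficial. The documents do not support that. Average bias needs unequal mortality, and its sign depends on whether deaths come before or after typical weaning.

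**What to change.** Make the primary test for each outcome a Wilcoxon rank sum test in which death before coming off iNO (or, for the second outcome, off invasive ventilation) receives the worst rank. Drop the t-test option for these two outcomes. Treat the secondary durations in the same way.

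An alternative is iNO-free and ventilator-free hours to a pre-stated day, with death scored 0. It is not equivalent: it needs a fixed horizon, which the article does not give for these outcomes, and it ties infants still on support at that day with those who died.

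State whether each duration continues or stops at ECMO. If it stops, rank ECMO as a failure.

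Report by arm, beside the primary result: deaths, ECMO, and survivors' durations with their SD in hours. Worst ranks yield no SD in hours, so this keeps the figure that the pilot is meant to supply for the definitive trial. It must be labelled as the SD among survivors.

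The cost is a change to the definition and analysis of the primary outcome, with no added infants or procedures. The downside is that the primary result then mixes death with duration, so it cannot be interpreted without its components beside it.
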